- fatigue
- muscle pain
- headache
- vomiting
- diarrhoea
- skin rash.

If COVID-19 is suspected, the volunteer will have a SARS-CoV-2 RNA test at home (throat swab) using the PCR to detect the SARS-CoV-2 infection. In 3 days, the test will be repeated. Any positive result will be considered as a confirmed COVID-19 case.

If COVID-19 is confirmed, the volunteer will be required to report this to a local outpatient clinic or other medical institution, where he/she receives medical care. Further follow-up of the volunteer will be performed at the outpatient medical institution. After the recovery and required self-isolation period, the subject may resume visits to the trial site to undergo procedures scheduled according to the Protocol. To the first visit after the recovery, the volunteer should bring a discharge summary issued by the medical institution, where he/she has been receiving medical care due to the confirmed COVID-19 case.

The study doctor will record the information about the COVID-19 case on a separate form of the subject’s CRF including the following information:

- onset and end dates
- severity:
- mild
- moderate
- severe
- extremely severe
- need for hospitalisation (yes/no/unknown)
- fatality (yes/no/unknown).

To collect the information, additional phone calls may be made.

Analysis of confirmed COVID-19 cases is the exploratory efficacy endpoint and they should not be registered as adverse events.

- 1. Assessment of Safety
     1. Specification of Safety Parameters

The list of safety parameters is provided in section 5.3.2.

- - 1. Methods and Timing for Assessing, Recording, and Analysing Safety Parameters
       1. Reactogenicity Evaluation

The evaluation of reactogenicity is performed by the investigator during visits on the day of vaccination and within the following 7 days (Visit 1/Day 0 (in 20 minutes (± 5 minutes), 2 hours (± 10 minutes), and 5–8 hours after vaccination), Visit 2/Day 2, Visit 3/Day 7) as a part of the registration of adverse events.

Reactogenicity of the investigational product will be evaluated by the study doctor according to local (injection site) and general (systemic) reactions to the vaccine administration. These reactions are expected reactions to the investigational vaccine administration, and they should be assessed for all study subjects.

Local reactions include redness, swelling, tightness/infiltration, pain, itching, arm weakness.

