| Biochemistry | Screening, Day 2, Day 28 | Total protein, alanine aminotransferase (ALT), aspartate aminotransferase (AST), alkaline phosphatase (ALP), lactate dehydrogenase (LDH), total bilirubin, creatinine, urea, fasting glucose, C-reactive protein |
| Coagulation test | Screening, Day 2, Day 28 | Activated partial thromboplastin time (aPTT), prothrombin time (PT), fibrinogen |
| Urinalysis | Screening, Day 2, Day 28 | Specific gravity, pH, protein, glucose, erythrocytes, leucocytes, casts |

- - - 1. Blood IgE test

Evaluation of the IgE level will be carried out to assess the allergenic effect of the investigational products. Blood sampling will be performed during the screening period and on Day 28.

The analysis will be carried out at the central laboratory using the EIA. The investigators will be provided with a separate laboratory manual containing detailed instructions on handling biological samples (collection, storage and transportation).

- - - 1. Adverse Events

An adverse event (AE) is defined as any untoward medical occurrence in a clinical study subject administered a pharmaceutical product and which does not necessarily have a causal relationship with this treatment.

An adverse event can therefore be any unfavourable and unintended sign, symptom (including an abnormal laboratory finding), or disease temporally associated with vaccination (not registered in a volunteer before the study or occurring during the study, or, if pre-existing, worsening during the study after vaccination with investigational products), whether or not causally related to the investigation product.

An adverse drug reaction means any adverse event, the causal relationship of which with vaccination with the investigational products is assessed at least as possible (possible, probable, definite), i.e. the relationship cannot be ruled out.

An unexpected adverse drug reaction is an adverse event, the nature or severity of which is not consistent with the applicable vaccine information provided in the Investigator’s Brochure.

A serious adverse event (SAE) is any adverse event that:

- results in death
- life-threatening
- requires inpatient hospitalisation or prolongation of existing hospitalisation except for planned hospitalisation (before this study), in-hospital treatment of the AE not considered as a SAE and not resulted in hospitalisation, or social admission
- results in persistent or significant disability/incapacity

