- is a congenital anomaly/birth defect in a neonate/infant born to a subject exposed to the investigational product.

Life-threatening means that the volunteer has been at risk of death at the time of the adverse event in the opinion of the investigator. This does not include events that could theoretically result in the volunteer’s death if they would be more severe.

Persistent or significant disability/incapacity means an event resulted in persistent or significant interference with normal daily activities.

Moreover, serious adverse events may include important medical manifestations, if based on the medical experience the investigator believes that without medical intervention the manifestation may lead to one of the above outcomes. Examples of such events are intensive treatment in an emergency room or at home for allergic bronchospasm or convulsions that do not result in hospitalisation.

A serious unexpected adverse drug reaction (SUADR) is a serious adverse drug reaction, the nature and severity of which is not consistent with the applicable product information provided in the Investigator’s Brochure.

1. Methods for Identification and Registration of Adverse Events

The investigator is responsible for AE registration during the clinical study.

It is necessary to register AEs identified in volunteers from the time of vaccination until the end of the study. From Visit 0 to Visit 5, all AEs should be registered. From Visit 5 to Visit 6, only SAEs should be registered. Adverse events should be registered sequentially as they occur.

Adverse events are recorded based on complaints reported by the volunteer him/herself, results of an interview of the investigator with the volunteer, results of the general or instrumental examinations, and laboratory tests. The investigator will formulate his/her questions in such a way that they do not provoke volunteers to report false information. For example, a question such as “Have any aspects of your health changed since the last visit/interview?” may be asked.

All adverse events should be documented in the source documents and CRF on the Adverse Events form.

The following information will be specified upon registration of an adverse event:

- subject’s identification number
- nature of the adverse event (it is preferable to state the diagnosis, not the list of symptoms)
- date of onset and resolution of the event (and time if applicable)
- AE severity according to the investigator

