- Possible — available data confirm the causal relationship with the vaccine administration; it may also relate to any concurrent disease or administration of any drug product.
- Doubtful — manifestations of the AE are not temporary related to the vaccine administration; there are other factors (drugs, diseases, chemical compounds) that may be the reason for their occurrence.
- Not related — AE does not occur within the acceptable time interval after the vaccine administration; it may be explained by other diseases or administration of other drug products.
- Unknown — it is not possible to assess the causal relationship with the vaccine administration due to limited information and reasons for the clinical manifestation.

An AE is considered related to vaccination if the causal relationship is assessed at least as possible (possible, probable, definite), i.e. the relationship cannot be ruled out.

1. Assessment of Adverse Event Outcome

An outcome of an adverse event should be recorded in the source documents and subject’s CRF using the following categories:

- resolved
- resolving
- not resolved
- resolved with sequelae
- death
- unknown.

1. Follow-up of Adverse Events

If an adverse event or its complications are not resolved, the investigator should follow up the volunteer. The adverse event or its complications should be followed up until their resolution or stabilisation (judged acceptable by the investigator), or until the determination of the reason of such adverse event not related to the use of the investigational product.

1. Investigator’s Responsibilities on Reporting of Serious Adverse Events

The investigator should immediately report on all SAEs developed in the volunteers from the time of vaccination until the end of the study. In the case of an SAE, the investigator should:

- Provide the volunteer with necessary medical care.
- Complete the SAE reporting form and send it via fax or email to the Qualified Person for Pharmacovigilance (QPPV) within not more than 24 hours from the moment of its discovery.
- Inform the LEC of the medical institution within the period specified in the committee regulations.

If additional information about the SAE becomes available that has not been included in the initial SAE report, it is necessary to complete the second SAE report with the indication of such information and send it to the QPPV within 24 hours.

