Before sending the SAE report, it is necessary to inform the QPPV or study monitor about the fax or email by phone.

If investigators have any additional questions, they should contact the study monitor of the trial site or the QPPV.

In the case of registration of an SAE related to the use of the investigational product, the report must be submitted even if the study has been completed.

Requests to provide further information received after the initial SAE report must be forwarded to the trial site by the QPPV (directly or through the monitor of the trial site) not later than 5 (for SAEs related to the study drug) or 30 (for SAEs not related to the study drug) days and continue with the same frequency until the complete resolution of the SAE or stabilisation of the subject’s condition.

| In the case of a serious adverse event, the appropriate SAE form should be immediately completed and sent by fax and/or email to the Qualified Person for Pharmacovigilance (QPPV):  [contact]  E-mail: [contact], [contact] |
| --- |

1. Other Investigator’s Reports

The investigator should report to the LEC of the medical institution on serious unexpected adverse drug reactions (SUADR) presumably related to the investigational product and other aspects of the treatment safety, which are subject to immediate reporting, including if they may influence the risk-benefit assessment of the vaccine or require significant changes in the study methodology.

1. Sponsor’s Responsibilities to Provide Safety Information in the Study

Reporting of Serious Unexpected Adverse Drug Reactions (SUADR) Presumably Related to the Investigational Product

The QPPV will be submitting expedited reports on SUADRs to regulatory authorities.

The QPPV will be also reporting to investigators on all SUADRs registered during the study.

SUADRs that lead to death or may be life-threatening for a volunteer should be submitted to regulatory authorities within not more than 7 calendar days once the information on such event is obtained by the QPPV, and second reports with the necessary additional information should be submitted within the following 15 calendar days.

Submission of Other Treatment Safety Reports

- The QPPV will be submitting to regulatory authorities expedited reports on other aspects of vaccination safety if they affect the risk-benefit assessment of the vaccination or may require significant changes in the dosing regimen or study methodology.

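### The protocol defines unexpectedness by nature or severity for reactions but by nature and severity for SUADRs, leaving the automatic expedited route ambiguous when only one departs from the Investigator's Brochure

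*Protocol*

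**What the plan says.** Two definitions stand close together in protocol section 8.4.2.8 (Adverse Events). The general one reads: "An unexpected adverse drug reaction is an adverse event, the nature or severity of which is not consistent with the applicable vaccine information". The reference text is the Investigator's Brochure, and either departure is enough. A little further on, a SUADR is defined as a "serious adverse drug reaction, the nature and severity of which is not consistent with the applicable product information", again with the Brochure as reference. This definition joins nature and severity with *and*, and it does not refer back to the general one.

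The reporting rules follow later in the same section. Under the sponsor's responsibilities, "The QPPV will be submitting expedited reports on SUADRs to regulatory authorities". The QPPV must also report all SUADRs to investigators. Fatal or possibly life-threatening SUADRs carry a fixed limit: they "should be submitted to regulatory authorities within not more than 7 calendar days" of the QPPV learning of the event. A separate provision covers "expedited reports on other aspects of vaccination safety if they affect the risk-benefit assessment of the vaccination or may require significant changes" to the dosing regimen or study methodology.

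Under the investigator's responsibilities, "The investigator should immediately report on all SAEs developed in the volunteers from the time of vaccination until the end of the study". The form goes to the QPPV within 24 hours, and the local ethics committee (LEC) is informed within its own time limits.

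Section 8.4.2.1 (Reactogenicity Evaluation) says of the local and general reactions to the vaccine: "These reactions are expected reactions to the investigational vaccine administration, and they should be assessed for all study subjects".

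**The concern.** The rules for automatic sponsor reporting use the SUADR label, not the general definition of unexpectedness. If the SUADR definition is narrower, it decides what must be sent out and by when.

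The case most exposed is a serious related reaction of a type already described, in a form more severe than described. Under the general definition it is unexpected because its severity departs. Under a literal *and* it is not a SUADR, because its nature does not depart. The wording in section 8.4.2.1 adds to the risk: a reader who sees fever or dyspnoea called an expected reaction may treat the question of expectedness as closed, severity included.

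At stake is the time-limited part of safety reporting, and what investigators at the other sites are told (about 10 sites are planned, section 5.1), in a trial whose interim report goes to regulators for a registration decision.

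**Working it through.** No sample size, power, alpha or event count is involved, so this is a check of the text.

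**Step 1: compare the definitions.** Take a serious adverse drug reaction. Let N mean that its nature is not consistent with the Brochure, and S that its severity is not. The general definition is met when N or S holds. The SUADR definition, read literally, is met when N and S both hold.

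| Nature departs (N) | Severity departs (S) | Unexpected (N or S) | SUADR, literal (N and S) | Agree? |
|---|---|---|---|---|
| No | No | No | No | Yes |
| No | Yes | Yes | No | **No** |
| Yes | No | Yes | No | **No** |
| Yes | Yes | Yes | Yes | Yes |

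The general rule flags 3 of 4 combinations, the literal SUADR rule 1 of 4, and they disagree in 3 − 1 = 2. These are counts of logical cases, not frequencies. The third row should rarely arise: if the Brochure does not describe a type of reaction, it normally gives no severity for the reaction to match. The second row, known type with greater severity, is the one that matters.

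**Step 2: trace that case through the reporting rules.**

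| Duty | Depends on SUADR status? | Second-row case, literal reading |
|---|---|---|
| Investigator reports the SAE to the QPPV within 24 hours | No, all SAEs | Kept |
| Investigator informs the LEC of the SAE | No, all SAEs | Kept |
| QPPV sends an automatic expedited report to regulators | Yes | Lost |
| 7-calendar-day limit, fatal or life-threatening | Yes | Lost |
| QPPV reports to investigators | Yes | Lost |
| QPPV sends an expedited report to regulators on other safety aspects | No, but conditional on effect on risk-benefit or need for significant changes | Possible; no day limit stated |

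**Step 3: look for text that settles the conflict.** None was found. The SUADR definition stands alone, and the reporting rules use the label without restating the test.

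**The case against.** The strongest reply is that the narrow reading is not the only one. The term SUADR contains the words for an unexpected adverse drug reaction, which the same section has just defined with *or*. The phrase joining nature and severity takes a singular verb and can be read as saying that the profile as a whole does not match. An experienced pharmacovigilance officer would probably read it so. This stands as far as it goes: the narrow reading is possible, not proven. But if two fair readings give different reporting duties, the text needs repair.

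Three stronger conclusions are tempting, and the protocol does not support them.

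- *Such a reaction falls outside expedited reporting altogether.* It does not. The provision on other safety aspects needs no SUADR status, and a fatal or life-threatening related reaction of unprecedented severity is an obvious candidate. Every SAE also reaches the QPPV and the LEC whatever its expectedness. What may be lost is the automatic route, its fixed limit and the stated duty to inform investigators.
- *Every reaction listed for reactogenicity is barred from SUADR status at any severity.* The list has 6 local and 12 general reactions, 18 in all. But both definitions test against the Brochure, which is not at hand, and section 8.4.2.1 does not say that all 18 are in it. The protocol also prefers a diagnosis to a list of symptoms, so a fatal event that presents with dyspnoea may be recorded under a term not on the list.
- *Earlier trials show cases that would have been missed.* At this dose the severe (Grade 3) reactions were fevers, in 2 of 36 participants in Phase I and 1 of 129 in Phase II. Severe is not serious: the protocol reports no SAE in Phase I up to 30 April 2020 and none in Phase II within 28 days. Nor does it give any ground for ranking an extreme form of a known reaction as the likeliest signal for this vaccine class.

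**Conclusion.** The conflict is real and can be checked from the text alone. Unexpectedness is defined with *or* in one place and with *and* in another, and the automatic reporting duties rest on the second. On the literal reading, a serious related reaction of known type but greater severity is unexpected yet not a SUADR. It may then lose three things: the automatic expedited report to regulators, the 7-calendar-day limit if fatal or life-threatening, and the QPPV's report to other investigators. It keeps the 24-hour report to the QPPV, notice to the LEC and the conditional route to regulators.

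This rests on a literal reading of *and* and on the Brochure describing the type of reaction at a lesser severity. How many reports would be affected cannot be estimated from the protocol. This is an internal contradiction in a safety-reporting trigger, and it touches no endpoint, sample size, power or alpha. It should be corrected because the trigger governs time-limited reports and the correction is cheap.

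**What to change.** Reconcile the two definitions in section 8.4.2.8. The simplest way is to define a SUADR as a serious adverse drug reaction that is unexpected as already defined there, which comes to replacing *and* with *or* between nature and severity. Add one sentence to section 8.4.2.1 saying that calling the listed reactions expected does not settle whether their severity is expected, which is judged case by case against the Investigator's Brochure.

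The cost is one word and one sentence in the protocol, and possibly a few more expedited reports. No statistical quantity changes.

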**Temperature Response**

The severity of temperature response (axillary body temperature increase) should be assessed using the table below.

Table 17 Temperature Response Severity Assessment

|  | **Mild (Grade 1)** | **Moderate (Grade 2)** | **Severe (Grade 3)** | **Life-threatening (Grade 4)** |
| --- | --- | --- | --- | --- |
| Fever (axillary body temperature increase) | 37.1–38.4 | 38.5–38.9 | 39.0–40 | > 40 |

Local and Systemic Reactions to the Vaccination (Reactogenicity Assessment), Other Clinical and Laboratory Abnormalities

The assessment of adverse event severity should be performed according to the FDA Guidance on Toxicity Grading Scale for Healthy Adult and Adolescent Volunteers Enrolled in Preventive Vaccine Clinical Trials (September 2007), https://www.fda.gov/media/73679/download

Tables to grade the severity of reactogenicity and other clinical and laboratory abnormalities from this guidance in English is provided in Appendix 1.

Other Adverse Events

The severity of adverse events not related to body temperature and not listed in Appendix 1 (as well laboratory abnormalities if the grading according to Appendix 1 is not possible) should be determined by the investigator based on the following criteria:

- Mild (Grade 1) — transient AE that does not require treatment or therapeutic intervention and does not interfere with the daily activity of the subject.
- Moderate (Grade 2) — AE that causes some interference with activity and does not require treatment.
- Severe (Grade 3) — AE that prevents daily activity and requires medical intervention.
- Life-threatening (Grade 4) — an immediate threat to life or AE leading to permanent mental or physical conditions that require ER visit or hospitalisation.

1. Causal Relationship of Adverse Events with Vaccination

Investigator’s opinion of the causal relationship of an AE to the investigational vaccine should be based on clinical information available at the time of the completion of the CRF.

The causal relationship should be graded according to the following scale:

- Definite — clinical manifestations develop within a specific time interval after the vaccine administration and cannot be explained by any concurrent disease or administration of other drug products.
- Probable — available data confirm causal relationship with the vaccine administration; the influence of any concurrent disease or administration of other drug products is unlikely.
- Possible — available data confirm the causal relationship with the vaccine administration; it may also relate to any concurrent disease or administration of any drug product.
- Doubtful — manifestations of the AE are not temporary related to the vaccine administration; there are other factors (drugs, diseases, chemical compounds) that may be the reason for their occurrence.
- Not related — AE does not occur within the acceptable time interval after the vaccine administration; it may be explained by other diseases or administration of other drug products.
- Unknown — it is not possible to assess the causal relationship with the vaccine administration due to limited information and reasons for the clinical manifestation.

An AE is considered related to vaccination if the causal relationship is assessed at least as possible (possible, probable, definite), i.e. the relationship cannot be ruled out.

1. Assessment of Adverse Event Outcome

An outcome of an adverse event should be recorded in the source documents and subject’s CRF using the following categories:

- resolved
- resolving
- not resolved
- resolved with sequelae
- death
- unknown.

1. Follow-up of Adverse Events

If an adverse event or its complications are not resolved, the investigator should follow up the volunteer. The adverse event or its complications should be followed up until their resolution or stabilisation (judged acceptable by the investigator), or until the determination of the reason of such adverse event not related to the use of the investigational product.

1. Investigator’s Responsibilities on Reporting of Serious Adverse Events

The investigator should immediately report on all SAEs developed in the volunteers from the time of vaccination until the end of the study. In the case of an SAE, the investigator should:

- Provide the volunteer with necessary medical care.
- Complete the SAE reporting form and send it via fax or email to the Qualified Person for Pharmacovigilance (QPPV) within not more than 24 hours from the moment of its discovery.
- Inform the LEC of the medical institution within the period specified in the committee regulations.

If additional information about the SAE becomes available that has not been included in the initial SAE report, it is necessary to complete the second SAE report with the indication of such information and send it to the QPPV within 24 hours.

Before sending the SAE report, it is necessary to inform the QPPV or study monitor about the fax or email by phone.

If investigators have any additional questions, they should contact the study monitor of the trial site or the QPPV.

In the case of registration of an SAE related to the use of the investigational product, the report must be submitted even if the study has been completed.

Requests to provide further information received after the initial SAE report must be forwarded to the trial site by the QPPV (directly or through the monitor of the trial site) not later than 5 (for SAEs related to the study drug) or 30 (for SAEs not related to the study drug) days and continue with the same frequency until the complete resolution of the SAE or stabilisation of the subject’s condition.

| In the case of a serious adverse event, the appropriate SAE form should be immediately completed and sent by fax and/or email to the Qualified Person for Pharmacovigilance (QPPV):  [contact]  E-mail: [contact], [contact] |
| --- |

1. Other Investigator’s Reports

The investigator should report to the LEC of the medical institution on serious unexpected adverse drug reactions (SUADR) presumably related to the investigational product and other aspects of the treatment safety, which are subject to immediate reporting, including if they may influence the risk-benefit assessment of the vaccine or require significant changes in the study methodology.

1. Sponsor’s Responsibilities to Provide Safety Information in the Study

Reporting of Serious Unexpected Adverse Drug Reactions (SUADR) Presumably Related to the Investigational Product

The QPPV will be submitting expedited reports on SUADRs to regulatory authorities.

The QPPV will be also reporting to investigators on all SUADRs registered during the study.

SUADRs that lead to death or may be life-threatening for a volunteer should be submitted to regulatory authorities within not more than 7 calendar days once the information on such event is obtained by the QPPV, and second reports with the necessary additional information should be submitted within the following 15 calendar days.

Submission of Other Treatment Safety Reports

- The QPPV will be submitting to regulatory authorities expedited reports on other aspects of vaccination safety if they affect the risk-benefit assessment of the vaccination or may require significant changes in the dosing regimen or study methodology.
- In addition to submission of expedited reports, the Sponsor will be preparing annual reports on vaccine safety throughout the whole study, including all new information obtained during the reported period. Such reports will be submitted to regulatory authorities at least once a year or with other intervals at the request of such authorities.

1. Pregnancy

The pregnancy itself is not an adverse event, except when there are grounds to believe that the administration of the investigational product has led to reduced efficacy of contraceptives. Any congenital anomalies and malformations in children of the volunteers are serious adverse events. Scheduled abortions carried out by medical indications, as well as any serious complications during the pregnancy (including spontaneous abortions), will be recorded as serious adverse events. Scheduled abortions without complications are not adverse events.

All pregnancies recorded during the study (including pregnancies of sex partners of the volunteers taking part in the study) will be properly registered.

In the case of confirmed pregnancy, the investigator should notify the contract research organisation/Sponsor about it within not more than 24 hours after obtaining the information by sending a completed pregnancy report form. Then, the information on the pregnancy outcome should be submitted. Pregnancy will be registered from the time of the vaccine administration until the last procedure conducted during the study.

The outcome of each pregnancy case (spontaneous abortion, elective abortion, birth of a normal child or a child with congenital anomalies or malformations) must be also registered.

During the collection of medical history at screening, pregnancies occurred within 30 days before vaccine administration should be registered and evaluated.

- - 1. Acceptability of Endpoints

Methods of efficacy evaluation selected for this trial are widely used during clinical and epidemiology studies of vaccines. As far as there are no special criteria to evaluate vaccine efficacy against novel coronavirus infection COVID-19, the criteria used in the previous studies of Ad5- nCoV have been chosen. The safety assessment methods used in this trial are generally accepted for clinical trials of vaccines.

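### The causality scale contradicts the protocol's own test for a related event: Unknown is left off the related list, and Possible demands confirming data

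*Protocol*

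**What the plan says.** Section 8.4.2.8.3 has six causality levels: Definite, Probable, Possible, Doubtful, Not related and Unknown. The rule beneath them reads: "An AE is considered related to vaccination if the causal relationship is assessed at least as possible (possible, probable, definite"), followed by the explanation that a link has not been excluded. Section 8.4.2.8 defines an adverse drug reaction by the same test, as an event whose relationship "is assessed at least as possible (possible, probable, definite), i.e. the relationship cannot be ruled out".

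The levels that matter here are worded as follows:
- Probable: "available data confirm causal relationship with the vaccine administration", with another cause unlikely.
- For Possible the text is "available data confirm the causal relationship with the vaccine administration; it may also relate to any concurrent disease or administration of any drug product", which repeats the confirmation test.
- Doubtful requires that timing does not fit and that other factors could account for the event.
- Unknown: "it is not possible to assess the causal relationship with the vaccine administration due to limited information".

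Section 8.4.2.8 then builds the reporting category on this: "A serious unexpected adverse drug reaction (SUADR) is a serious adverse drug reaction" that is not consistent with the Investigator's Brochure. Under section 8.4.2.8.8, SUADRs trigger expedited reports to regulators, a 7-calendar-day limit for fatal or life-threatening cases, and notices to all investigators. Section 8.4.2.8.6 sets a limit of 5 days for follow-up queries on related serious adverse events (SAEs) and 30 days for those not related. Section 9.2.4 tabulates all AEs and SAEs, with relationship to vaccination as one breakdown.

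**The concern.** A list and its own explanation should select the same events. Here they do not. For an Unknown event the list answers no, while the explanation answers yes, because a link that could not be assessed has not been excluded. For Possible, the lowest level that counts as related, the wording asks for confirmation, which is far more than the explanation asks for.

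The list decides what is an adverse drug reaction, hence what can be a SUADR. Causality is rated on the information at hand when the CRF is completed, so an early report of a serious event that is still being worked up is a likely candidate for Unknown. At stake are the consistency of regulatory safety reporting and the count of vaccine-related events in a trial whose interim safety data go to regulators for a registration decision.

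**Working it through.** No arithmetic applies. The protocol gives no figure on this point, and the question is one of definitions. I set the levels side by side and followed each to its consequences.

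**Step 1. What each level requires, and whether it is on the related list.**

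| Level | Timing | Evidence or other cause | On list? |
| --- | --- | --- | --- |
| Definite | fits | not explained by another disease or drug | yes |
| Probable | not stated | data confirm; other cause unlikely | yes |
| Possible | not stated | data confirm; other cause may apply | yes |
| Doubtful | does not fit | other factors may be the reason | no |
| Not related | does not fit | may be explained by other causes | no |
| Unknown | not stated | cannot be assessed, limited information | no |

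**Step 2. The Unknown row.** Not assessable implies not excluded. The explanation attached to the list therefore covers Unknown, and the list omits it.

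**Step 3. The gap around Possible.** Take an event with plausible timing, a concurrent illness that might explain it, and no data confirming a vaccine effect.
- Definite fails, because another explanation exists.
- Probable and Possible fail on the confirmation wording.
- Doubtful and Not related fail, because the timing fits.
- Unknown applies only if information is limited, and here it need not be.

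This is the ordinary case for a Possible rating, and read literally it has no level. An event with plausible timing and no other explanation is not caught in this gap, because Definite takes it.

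**Step 4. Consequences of an Unknown rating for a serious unexpected event.**
- Adverse drug reaction (8.4.2.8): not met by the list.
- SUADR (8.4.2.8): not met, because it is a subset of adverse drug reactions. The SUADR report, the 7-day limit for fatal or life-threatening cases and the notices to investigators (8.4.2.8.8) are therefore not triggered.
- Query interval (8.4.2.8.6): 5 days applies to related SAEs and 30 days to not-related SAEs. Unknown is assigned to neither.
- Report after study completion (8.4.2.8.6): expressly required for related SAEs. Unknown is not mentioned.
- SAE report to the Qualified Person for Pharmacovigilance (QPPV) within 24 hours (8.4.2.8.6): still required, whatever the causality.
- Expedited report on other safety aspects that bear on risk-benefit (8.4.2.8.8): still available.
- AE and SAE tables (9.2.4): the event stays in. Only a count of related events would leave it out.

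**The case against.** The case on the other side has several parts, and much of it stands.

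**Unknown is never called unrelated.** A reader might infer that the protocol counts Unknown events as unrelated. No sentence says so. The exclusion follows from omission, and the explanation after the list can be read the other way. That narrows the point without removing it: two readings that give opposite answers for the same event still need reconciling.

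**Nothing leaves the tables.** A reader might also infer that such events vanish from the safety tables. Section 9.2.4 tabulates all AEs and SAEs and describes no table restricted to adverse drug reactions. Local and systemic reactions are summarised separately, with no stated causality filter. Investigators are blinded, so the scale is applied alike in both arms, and the comparison of all AEs is untouched. How Unknown is grouped in tables may also be settled in a statistical analysis plan that is not shown.

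**A sensible investigator would use Possible anyway.** Its wording goes on to allow a competing cause, and the rule below softens it. The confirmation wording may come from translation. This is plausible, but it relies on the reader to override the operative text at the level that separates related from unrelated.

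**The safety net is real.** All SAEs reach the QPPV within 24 hours, new information needs a further report within 24 hours, and unresolved events are followed up. However, the 24-hour report goes to the QPPV rather than to regulators, and the risk-benefit route depends on judgement and has no stated deadline.

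**No count can be given.** It is tempting to apply an assumed share of Unknown ratings to the Phase II AE rate. The documents give no such share. That rate is also the wrong base: in the 5x10^10 VP arm 98 of 129 had any AE within 28 days and 96 of 129 had a solicited reaction within 14 days. Section 8.4.2.1 treats local and general vaccine reactions as expected, so they are the least likely to be rated Unknown.

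**Conclusion.** The contradiction holds on the face of sections 8.4.2.8 and 8.4.2.8.3. The related list omits a level that satisfies its own explanation, and Possible is worded more strictly than that explanation. As written, a serious unexpected event rated Unknown does not meet the SUADR trigger and has no assigned query interval, and a common type of event has no level that fits. Only the related count and the SUADR route, with the query and post-study rules tied to relatedness, are affected. The overall AE and SAE tables, 24-hour SAE reporting and the risk-benefit route are not.

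The size cannot be stated as a number of events. For serious events, one Unknown rating is enough to matter. The conclusion rests on reading the list as closed. If the explanation is taken to govern instead, Unknown events would count as related, and the list would then be the part that is wrong. The primary endpoint, sample size and error rate are unaffected. The point is worth correcting because it concerns safety reporting and the correction is small.

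**What to change.** Reconcile sections 8.4.2.8 and 8.4.2.8.3, and carry the change into the CRF completion instructions.

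1. Reword Possible to match the protocol's own criterion: the timing is plausible, a link to vaccination has not been excluded, and a concurrent disease or another drug may also explain the event. The other levels can stay.
2. State that Unknown or missing causality is handled as not excluded for SUADR reporting and for the query interval until the event is reclassified.
3. In the safety tables show Unknown as its own row, and give the related count with and without it. Counting Unknown as related in every analysis is only one convention, so two counts are better than a fixed choice.

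The cost is about two sentences in the protocol, one extra table row and possibly a few more expedited reports.
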